#### Secondary outcomes

Speech understanding (especially in noise) reflects a patient’s ability to communicate in everyday and working life better than pure tone threshold. However, the results of speech audiometry in different languages cannot easily be compared and are also influenced by other parameters such as speech competence. Speech audiometry tests are also difficult to interpret in patients whose native language is not that of the test lists.

Different categories of improvement based on change in pure tone or speech reception threshold have been suggested (e.g., [4, 13, 17, 36, 38] among others). A clinical practice guideline recognizes that fixed levels of improvement “… may have different benefits for different patients …” [38]. Therefore, speech audiometry and categories of improvement will be used as secondary outcome measures in this study. The recovery category is defined based on the pure tone average 30 days after start of therapy and referenced to the pre-event audiogram, the audiogram of the unaffected ear, or the ISO age- and sex-corrected standard audiogram: deterioration (> 10 dB increase, i.e., worsening), no change (≤ ±10 dB change), partial recovery (> 10 dB increase, i.e., improvement but not ≤ 10 dB difference to reference audiogram), and complete recovery (≤ 10 dB difference to reference audiogram). Most international trials and classifications of hearing improvement use 10 dB as a criterion for “partial improvement” (summary in [29], recommendation in [38]). The 10-dB criterion is based on the 5‑dB resolution of the method (ISO 8253-1), the test-retest reliability, and the clinical relevance of the hearing improvement.

As suggested by Stachler et al. [38] and others, for those patients with initial profound hearing loss (“non-serviceable hearing”) and partial recovery, it will be evaluated whether the hearing threshold resulted in “serviceable hearing,” meaning whether these patients would benefit from a conventional hearing aid. However, no international consensus exists with respect to hearing ability being “meaningful” or “serviceable.” There are different categories of hearing impairment. While the American Speech–Language–Hearing Association, according to Clark (1981), defines profound hearing loss as ≥ 91 dB, the WHO defines profound hearing loss with ≥ 80 dB pure tone average [7, 45]. There are no clear-cut criteria on whether a patient will benefit from using a hearing aid or not. The hearing level at which a hearing aid is useful covers a range of thresholds (see also WHO grades of hearing impairment [45]). Whether a hearing aid is used or not, and especially whether a cochlear implant is decided for, depends on a variety of objective and subjective factors, and on regional factors with respect to the world. However, since this is a patient-specific and socio-economically relevant aspect, the percentage of patients having received or being planned for rehabilitation with a hearing aid or a cochlear implant will be evaluated at a follow-up visit 6 months after ISSHL. In addition, subjective patient evaluation and quality of life will be assessed by means of the patients’ questionnaires that were selected in cooperation with three patient self-help groups (German Cochlear Implant Society [Deutsche Cochlear Implant Gesellschaft e.V., DCIG, Senden], German Alliance of Hearing Impaired [Deutscher Schwerhörigenbund e.V., DSB, Berlin], and German Society of Hearing Impaired [Deutsche Gesellschaft der Hörgeschädigten – Selbsthilfe und Fachverbände e.V., DG, Rendsburg]).

Arterial hypertension and impaired glucose tolerance are the two major adverse events following short-term high-dose glucocorticoid treatment. Alterations in glucose metabolism arise from enhanced hepatic gluconeogenesis and impaired glucose uptake by adipose tissues [35]. In healthy individuals, this rarely leads to relevant complications. However, in the presence of already impaired glucose tolerance, hyperglycemia may occur. The HOMA-IR is a useful index for detecting subclinical insulin resistance, which is more sensitive for detecting altered glucose metabolism than mere measurements of blood glucose [2].

Blood pressure effects of glucocorticoids are in part mediated by renal fluid retention and increased vascular responsiveness to catecholamines; however, additional unknown mechanisms seem to be involved [42]. Blood pressure elevations will be detected by 24‑h blood pressure measurements on day 5 of glucocorticoid treatment, where maximum effects are expected.

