## Assignment of interventions: allocation

### Sequence generation {16a}, concealment mechanism {16b}, and implementation {16c}

A computerized random algorithm using nQuery 7.0 was applied to generate the random allocation of the participants to one of the three study groups: group 1: i.v. prednisolone; group 2: i.v. dexamethasone; and group 3: oral prednisolone. To establish a balanced distribution of the therapy groups, a block-randomization with a fixed block size of 6 was used. The randomization was stratified for baseline PTA (< 81 dB vs. ≥ 81 dB, limit for profound hearing impairment according to WHO World Health Organisation 2008 Grades of Hearing Impairment). According to the randomization lists, an independent employee of the KKS Halle prepared packages including sets with study medication. Each package contained sets for three patients. The sets were numbered and looked equal irrespective of the mode of therapy included. The randomization details and the randomization lists were fixed in a separate document that is unavailable to anyone, involved in the enrolment, therapy application, data management, monitoring, and outcome assessments. The participating centers are centrally supplied with medication sets in such a way that each time a minimum of three sets are available. In the case of randomization, patients will be centrally assigned (information on the number of the study medication set) via an Internet-based automatic system by the Coordination Centre for Clinical Trials, University of Halle-Wittenberg, Halle (Saale).

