The clinical relevance of this MID, however, depends on the degree of initial hearing loss (i.e., moderate, severe, profound hearing loss) and whether the patients had serviceable hearing before and/or after therapy [38]. For example, a 10-dB change might not be useful in severe or profound hearing loss if the patient (or the ear) would remain at a cochlear implant candidate level after therapy. The U.S. clinical practise guideline therefore correctly recommends that future studies should report the number of patients reaching serviceable hearing: “… For ears that were rendered nonserviceable by the episode of SSNHL, return to serviceable hearing should be considered a significant improvement, and whether or not this level of recovery occurs should be recorded. Recovery to a serviceable level typically indicates that after recovery, the ear would be a candidate for traditional hearing amplification. Recovery to less than serviceable levels indicates an ear that would in most circumstances not benefit from traditional amplification. For ears with SSNHL to hearing levels that are still in the serviceable range, a 10 dB HL improvement in pure-tone thresholds (the smallest recordable improvement outside of the range of error for most audiograms) or an improvement in WRS of ≥ 10% (approximate lower limit for a statistically significant change based on binomial tables for WRS of > 50% at baseline) should be considered partial recovery and recorded …” (cited from [38]).

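### Return to serviceable hearing is evaluated only in initially profound ears with partial recovery, so an arm comparison would be conditioned on the day-30 result and omit complete recoveries

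*Protocol article*

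**What the plan says.** Four statements in the protocol article bear on this.

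- **Who is evaluated.** Secondary outcomes, citing the US practice guideline, takes patients with initially profound loss "and partial recovery, it will be evaluated whether the hearing threshold resulted in" serviceable hearing, explained as likely benefit from a conventional hearing aid. It adds that there is no consensus on what counts as serviceable and no clear-cut criterion for hearing-aid benefit.
- **When the category is set.** In the same section: "The recovery category is defined based on the pure tone average 30 days after start of therapy".
- **How the categories divide.** Partial recovery is a gain of more than 10 dB, "improvement but not ≤ 10 dB difference to reference audiogram". An ear within that distance belongs to the next category, "complete recovery (≤ 10 dB difference to reference audiogram". No ear can be in both.
- **What the guideline says.** The Discussion quotes it at length. For ears made nonserviceable by the episode, "return to serviceable hearing should be considered a significant improvement", and whether this level is reached should be recorded. No partial-recovery condition appears. The article agrees that trials should report how many patients reach serviceable hearing.

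Elsewhere, Hearing evaluation ({18a}) reports the proportions in all four recovery categories. Section {20a} lists no analysis of serviceable hearing and calls all secondary tests descriptive. Sections {20a} and {20b} plan subgroups at < 81 and ≥ 81 dB for primary and secondary endpoints.

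**The concern.** Whether a patient enters the evaluated set depends on the day-30 audiogram, which treatment may change. Randomization balances the arms among all initially profound ears. It does not balance them among those that later turn out to be partial recoveries. The selection also works against the best result: an initially profound ear that returns to within 10 dB of its reference leaves the set, so an arm that turns partial into complete recoveries takes its own successes out of both numerator and denominator.

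The item has a purpose. The Discussion notes that a 10-dB gain may be of little use in severe or profound loss if the ear remains at cochlear-implant level, and it turns to serviceable hearing to address this. A figure limited to partial recoveries does not tell the reader how many initially profound ears became serviceable in each arm, and it could point the wrong way.

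**Working it through.** The article gives no figure for serviceable hearing, so there is none to reproduce. The check has two steps.

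**Step 1: the text.** Partial and complete recovery are mutually exclusive and both are set at day 30. The evaluated set is initially profound and partial. It therefore excludes complete recoveries, no-change ears and deteriorations, and membership is decided after randomization. The guideline's set, as quoted in the Discussion, is all ears made nonserviceable by the episode. No statement in the article adds complete recoveries back to the serviceable-hearing item.

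**Step 2: what the restriction can do.** All counts below are assumed. Take 40 initially profound ears per arm, with C complete, S partial and serviceable, P partial and not serviceable, X other. Completely recovered ears are taken as serviceable. Three measures are compared:

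- share within partial recoveries: S/(S+P)
- partial and serviceable over all initially profound ears: S/40
- all serviceable over all initially profound ears: (C+S)/40

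| Scenario | C | S | P | X | S/(S+P) | S/40 | (C+S)/40 |
|---|---|---|---|---|---|---|---|
| 1. Control | 4 | 12 | 8 | 16 | 12/20 = 60.0% | 30.0% | 16/40 = 40.0% |
| 2. As 1, 4 ears move from S to C | 8 | 8 | 8 | 16 | 8/16 = 50.0% | 20.0% | 16/40 = 40.0% |
| 3. As 1, 8 ears move from S to C | 12 | 4 | 8 | 16 | 4/12 = 33.3% | 10.0% | 16/40 = 40.0% |
| 4. More serviceable ears overall | 12 | 6 | 8 | 14 | 6/14 = 42.9% | 15.0% | 18/40 = 45.0% |
| 5. As 1, 4 ears move from P to S | 4 | 16 | 4 | 16 | 16/20 = 80.0% | 40.0% | 20/40 = 50.0% |

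- Scenarios 2 and 3 only improve hearing relative to scenario 1, yet the restricted share falls from 60.0% to 50.0% and 33.3%. The all-ears rate stays at 40.0%.
- Scenario 4 against 1 reverses the direction: 42.9% against 60.0% restricted, 45.0% against 40.0% in all ears.
- Enlarging only the denominator does not help. S/40 falls from 30.0% to 20.0% and 10.0% in scenarios 2 and 3, because complete recoveries are still not counted.
- Scenario 5 shows that the restricted share is not always wrong. It moves in the right direction when the gain is from nonserviceable to serviceable within partial recovery.

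These percentages depend on the proportions, not on the choice of 40 ears.

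**The case against.** The strongest reply is that the article fixes no denominator, proportion, test or arm comparison for this item, and that the sentence may only subdivide the partial category, where serviceability is most in doubt. Complete recoveries are reported as their own category, and with the ≥ 81 dB subgroup planned for secondary endpoints, a reader might combine the two. Other measures carry no partial-recovery condition: hearing-aid or implant provision at 6 months, monosyllable scores and the quality-of-life questionnaires. Much of this stands. The subdivision reading is possible, but the text does not state it, and nothing says that the combined count will be reported.

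Stronger readings that a reader might infer are not supported:

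- **That a better arm will look worse.** The table shows only that it can. The article gives no recovery rates.
- **That leaving out gains of 10 dB or less is a plain error.** Secondary outcomes bases the 10-dB criterion on the 5-dB resolution, test-retest reliability and clinical relevance. The guideline text in the Discussion treats 10 dB as the smallest improvement outside measurement error. The choice is documented.
- **That the baseline limit is contradictory.** Secondary outcomes says "the WHO defines profound hearing loss with ≥ 80 dB pure tone average", while the randomization section uses 81 dB as the "limit for profound hearing impairment according to WHO". The former is one of two published definitions given as background, next to ≥ 91 dB. The operative limit is 81 dB in the randomization section, {20a} and {20b}. At most a citation is loosely worded. On a 5-dB grid, three-frequency means near the limit are 78.3, 80.0 and 81.7 dB, so only a mean of exactly 80.0 dB would be classed differently.

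**Conclusion.** The concern holds as a fault in how one secondary item is defined. As worded, the evaluated set is selected on a day-30 outcome and omits complete recoveries. A between-arm comparison within it would not be a randomized comparison and could mislead in direction. The set also departs from the guideline text that the article quotes and endorses, and does not yield the number of patients reaching serviceable hearing.

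The size of any distortion is unknown. The reversal (60.0% against 42.9% restricted; 40.0% against 45.0% in all ears) rests on assumed counts and on completely recovered ears being serviceable, which may fail where the reference hearing was already poor. The item is descriptive, complete recoveries are reported separately, and the primary analysis, which includes all randomized patients, is untouched.

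**What to change.** - Delete the partial-recovery condition. Report, by allocated arm, the proportion reaching serviceable hearing at day 30 among all randomized patients in the baseline ≥ 81 dB stratum, whatever their recovery category. Count complete recoveries that reach the serviceable range as successes.
- Prespecify one serviceable-hearing criterion before unblinding. It should not simply be a day-30 average below 81 dB: nothing in Secondary outcomes equates no longer profound with serviceable. One 5-dB step at one of three frequencies shifts the mean by 5/3 = 1.67 dB, so a move from 81.67 to 80.0 dB would count as success although it lies within measurement error.
- State whether crossing the criterion with a gain of 10 dB or less counts, given the measurement-error reasoning in Secondary outcomes and the Discussion.
- The split of partial recoveries into serviceable and not can stay as a description, if labelled as such.

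The cost is a short definition in the analysis plan, which Trial status says was still being finalized during blind review. The audiograms are already scheduled, so no new data are needed. The one real decision is the criterion, because the article itself says that no consensus exists.

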### Participant timeline {13}

For the time schedule of enrolment, interventions, assessments, and visits for participants, see Table 2.

**Table 2 Tab2:** Time schedule of enrolment, interventions, assessments, and visits for participants

	BL^a^			Therapy			Th. end	FU 1^b^	FU 2^b^
Visit	1	2	3	4	5	6	7	8	9
Day	−6 to 1	1	2	3	4	5	10–13	30 ± 4	180 ± 14
*Demographic data*	X	-	-	-	-	-	-	-	-
*Informed consent*	X	-	-	-	-	-	-	-	-
*Inclusion and exclusion criteria, medical history*	X	-	-	-	-	-	-	-	-
*Physical examination*^1^	X	-	-	-	-	-	-	-	-
*Laboratory assessments*^2^									
Complete blood count	X	-	-	-	-	-	-	-	-
Clinical chemistry tests	X	-	-	-	-	-	-	-	-
Pregnancy test	X	-	-	-	-	-	-	-	-
Blood sample (fasting) for central laboratory^3^	X^3^	-	-	-	-	X^3^	-	-	-
Shipment of samples to central laboratory	-	-	-	-	-	X	-	-	-
POCT-glucose (before medication)	X^c^	X^c^	X	X	X	X	X	X	X
*Audiological assessments*^4^									
Pure tone audiometry	X^c^	X^c^	-	X^5^	-	X^5^	X	X	X
Impedance audiometry	X	-	-	-	-	-	-	X	X
Speech audiometry	X^c^	X^c^	-	X^5^	-	X^5^	X	X	X
*Otoneurological assessment*^6^	X		-	-	-	-	-	-	-
*Blood pressure, pulse*	X^c^	X^c^	X	X	X	X	X	X	X
*Long-term blood pressure*	-	-	-	-	-	X^7^	-	-	-
*Study medication*									
Documentation of concurrent medication	X	X	X	X	X	X	X	X	X
Application of study medication i.v.	-	X	X	X	X	X	-	-	-
Dispensing of p.o. medication and instruction	-	X	-	-	-	X	-	-	-
*Documentation of adverse events (AEs)*	-	X	X	X	X	X	X	X	-
*Documentation of quality of life (QOL)*	X^c^	-	-	-	-	-	-	X	X
*Documentation of tinnitus*	X^c^	-	-	-	-	-	-	X	X
*Indication for hearing aid/cochlear implant*	-	-	-	-	-	-	-	X	X
*MRI*	X								
*CRF-documentation/drug accountability*	X	X	X	X	X	X	X	X	X

*POCT* point-of-care testing, *Th. end* end of drug therapy

^a^
*BL* baseline

^b^
*FU* follow-up, FU 1: primary endpoint

^c^ Assessments at visits 1 & 2 can be made on the same day, e.g., the patient may receive the first study medication on the day of enrolment. Assessment of baseline blood glucose, pure tone and speech audiometry, blood pressure, pulse, quality of life and tinnitus should not take place more than 1 day before the first study medication

^1^ Includes: physical examination of all organ systems, weight, size, ENT examination, body temperature

^2^ Includes: complete blood count, clinical chemistry tests (ALAT, ASAT, GGT, ALP, creatinine, sodium, potassium, calcium, CRP), pregnancy test (hCG)

^3^ Central laboratory evaluations: measurement of HbA1c (baseline only), insulin, HOMA-IR (baseline and V6), fasting if possible, blood sample must be taken before medication; if V6 Saturday or Sunday or holiday: blood sample may be taken at last or next working day

^4^ Pure tone audiogram 250–8000 Hz, bone and air conduction; impedance audiometry, speech (monosyllables at 65 and 80 dB SPL with Freiburger speech test)

^5^ If visit on Saturday, Sunday or holiday these assessments may be omitted

^6^ Includes: spontaneous nystagmus, caloric or head impulse test, Romberg test; may be done at V1 or V2, at V2 also after medication possible

^7^ Day 5 ± 2 days

### Sample size {14}

This three-armed trial (randomization ratio: 1:1:1) is aimed at comparing standard-dose systemic therapy with two types of high doses of systemic therapy concerning the primary endpoint using two individual statistical tests assuming a normal distribution of the primary endpoint in the population. For a global significance level of 0.05, we adjust for two tests using a local level for each test of 0.025. The following assumptions are based on the available literature [32]. A sample size of 88 in each group will have 80% power to detect a difference between high dose and standard dose, when the true difference in means is −10.0 (e.g., the difference between a group 1 mean, μ1, of 30.7 and a group 2 mean, μ2, of 40.7) assuming that the common standard deviation is 21.3. The sample size calculation was performed for two-sample *t* tests with nQuery Version 7.0. Assuming a dropout rate of approximately 15%, a total of 312 patients need to be randomized (1:1:1) to maintain at least 264 evaluable patients with complete data (high-dose dexamethasone: 104; high-dose prednisolone: 104, standard prednisolone: 104).

Systemic glucocorticoids are the standard treatment in ISSHL. Since the study drugs thus do not involve a completely new therapeutic concept, patient compliance is generally estimated as high. We assume a rate of loss to follow-up of 15%. This estimate is based on two recent RCTs on ISSHL. Nosrati-Zarenoe and Hultrantz (2012) randomized 103 patients and were able to analyze 88 (85%) on day 8 of the assessment and 73 (71%) at the 3‑month time point [26]. In the study of Rauch et al. (2011), 221 of 255 patients (87%) completed the intervention and 2‑month follow-up (per-protocol analysis [32]).

The trial will be analyzed according to the intention-to-treat principle including all randomized patients. A per-protocol analysis will be performed as sensitivity analysis.

### Recruitment {15}

There has been no pilot study carried out using this design. The estimated recruitment rate of approximately 25% is based on three recent multicenter RCTs on ISSHL and on our own experience [17, 26, 30, 32]. Potentially participating centers were selected based on self-estimated recruitment: All centers were evaluated at pre-study visits. The German Professional Association of ENT Surgeons (BV-HNO e.V.) and the German Society of Otorhinolaryngology, Head & Neck Surgery e.V., Bonn, regularly remind German ENT specialists about the trial and the inclusion criteria through e‑mail newsletters and in the societies’ publications for their members. The study is also advertised through the website of the German Study Center for Otolaryngology, Head and Neck Surgery (DSZ-HNO) and the funders homepage. Study centers with no or insufficient recruitment will be closed.

## Assignment of interventions: allocation

### Sequence generation {16a}, concealment mechanism {16b}, and implementation {16c}

A computerized random algorithm using nQuery 7.0 was applied to generate the random allocation of the participants to one of the three study groups: group 1: i.v. prednisolone; group 2: i.v. dexamethasone; and group 3: oral prednisolone. To establish a balanced distribution of the therapy groups, a block-randomization with a fixed block size of 6 was used. The randomization was stratified for baseline PTA (< 81 dB vs. ≥ 81 dB, limit for profound hearing impairment according to WHO World Health Organisation 2008 Grades of Hearing Impairment). According to the randomization lists, an independent employee of the KKS Halle prepared packages including sets with study medication. Each package contained sets for three patients. The sets were numbered and looked equal irrespective of the mode of therapy included. The randomization details and the randomization lists were fixed in a separate document that is unavailable to anyone, involved in the enrolment, therapy application, data management, monitoring, and outcome assessments. The participating centers are centrally supplied with medication sets in such a way that each time a minimum of three sets are available. In the case of randomization, patients will be centrally assigned (information on the number of the study medication set) via an Internet-based automatic system by the Coordination Centre for Clinical Trials, University of Halle-Wittenberg, Halle (Saale).

